#### Inclusion and Exclusion Criteria

The study inclusion criteria will be as follows: (1) a parent or guardian, or at least one person in the household, has a working Android-based smartphone, (2) the parent or guardian has a basic ability to use an Android-based smartphone, and (3) the parent or guardian provides consent. The study exclusion criterion is that the family does not plan to visit the AKUH for scheduled CRI visits when their child is 10 and 14 weeks of age.

#### Sample Population and Size

Target enrollment is 328 infants, 164 in each arm; assumptions used for calculating sample size are an increase in RCI coverage rate from 40% to 60%, power of 0.80, α error rate of .05, and allowing for 10% dropout [27].

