### Outcomes

#### Primary Outcomes

We aim to see the following primary outcomes: (1) a 10% increase in RCI through a personalized smartphone–based app at 10 and 14 weeks of age, according to the EPI schedule, versus standard care and (2) a 10% increase in RCI within 1 week of the original timeline at 10 and 14 weeks versus standard care.

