### Trial RCT

#### Study Design, Settings, and Timeline

The study design is an RCT, consisting of two parallel arms with the allocation of 1:1 to the intervention group or the standard care group (ie, control group). After obtaining informed consent, eligible infants and their caregivers will be randomly allocated into one of two groups using randomly generated computer assignments, where allocations will be placed in sealed opaque envelopes to be opened at the time of enrollment. IDs will be generated in blocks, with 6 cases in each block. Details of each group are as follows:

Intervention group: the intervention group, in addition to the standard counseling group, will receive text, voice, pictorial, and video messages regarding vaccinations; messages will be received once a week until the child turns 14 weeks of age.Control group: the control group will receive one-time, standard, verbal counseling at the time of the initial visit for on-time EPI vaccines at 10 and 14 weeks of age, as recommended by the EPI and the government of Pakistan.

The trial was registered at ClinicalTrials.gov (NCT04449107).

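### The 164 infants per arm does not follow from the inputs printed with it, which give about 108 to 119 per arm; an input is wrong or unstated

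*Protocol article*

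**What the plan says.** The Sample Population and Size section of the protocol article is one sentence. It fixes the size ("Target enrollment is 328 infants, 164 in each arm") and lists the assumptions: "an increase in RCI coverage rate from 40% to 60" percent, power of 0.80, "α error rate of .05" and "allowing for 10% dropout". It does not mention sidedness, a continuity correction, a division of α or any other inflation.

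Study Design, Settings, and Timeline describes "two parallel arms with the allocation of 1:1 to the intervention group or the standard care group". Randomization is individual, and Sampling Methodology takes one child per household, so there is no clustering that would call for a design effect.

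Primary Outcomes lists two outcomes, each tied to the 10- and 14-week visits. The second is "a 10% increase in RCI within 1 week of the original timeline at 10 and 14 weeks versus standard care". No division of α between them is given.

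**The concern.** The sentence presents 164 per arm as the result of four stated assumptions. A reader who puts those assumptions into the usual two-proportion formula gets a number about one third smaller. The gap is too large for rounding or choice of formula.

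The statement is what an ethics committee and later readers use to judge whether the number enrolled is justified. As printed, either the infants required for the stated aim are overstated, or the power is understated, or the significance level or effect used in the planning is not the one shown. The last possibility also bears on the analysis: if planning used a smaller α per comparison, the printed .05 does not tell the analyst so.

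**Working it through.** **Inputs** (Sample Population and Size): p₁ = 0.40, p₂ = 0.60, power 0.80, α .05, dropout 10%. Allocation is 1:1 (Study Design, Settings, and Timeline). Sidedness is not stated; two-sided is assumed and one-sided is also tried.

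**Attempt to reproduce 164.** The pooled-variance formula with p̄ = 0.50 is

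n = [z₁₋α/₂ √(2p̄(1−p̄)) + z₁₋β √(p₁(1−p₁) + p₂(1−p₂))]² / (p₂−p₁)²

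= [1.960 × 0.7071 + 0.842 × 0.6928]² / 0.04 = 1.969² / 0.04 = 96.9, so 97 per arm.

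With continuity correction:

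n_c = (n/4)[1 + √(1 + 4/(n × 0.20))]² = (96.9/4)[1 + √1.206]² = 106.7, so 107 per arm.

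After dropout, 97/0.9 = 107.8 and 107/0.9 = 118.9.

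| Version | Evaluable per arm | Per arm after dropout | Total |
|---|---|---|---|
| Two-sided, pooled | 97 | 108 | 216 |
| Two-sided, continuity-corrected | 107 | 119 | 238 |
| Two-sided, unpooled variance | 95 | 106 | 212 |
| Two-sided, arcsine | 97 | 108 | 216 |
| One-sided, pooled | 77 | 86 | 172 |
| One-sided, continuity-corrected | 86 | 96 | 192 |
| **Printed** | not stated | **164** | **328** |

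Multiplying by 1.1 instead of dividing by 0.9 gives 107 and 118 for the first two rows. No version is close to 164. The excess is 328 − 238 = 90 (38% of 238) to 328 − 216 = 112 (52% of 216). Reaching 164 from these evaluable numbers by dropout alone would need 1 − 107/164 = 35% to 1 − 97/164 = 41%, against the stated 10%.

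**Power that 164 per arm gives.** Evaluable per arm is 164 × 0.9 = 147.6, about 148. At two-sided α .05 for 40% versus 60%:

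- Uncorrected: (0.20 × √148 − 1.960 × 0.7071)/0.6928 = 1.51, so power is 93.5%.
- Continuity-corrected: 148 corresponds to an uncorrected 148 × (1 − 1/(148 × 0.20))² = 138.2, so power is 91.8%.

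**What would give about 164.** Each row departs from the printed inputs in the way shown.

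| Change | Evaluable per arm | After dropout |
|---|---|---|
| α .0125, with continuity correction | 147.8 (148) | 147.8/0.9 = 164.2 (from 148: 165, or 163 by × 1.1) |
| α .0125, without correction | 138 | 154, no match |
| α .01, without correction | 145 | 162, near |
| α .05, power about .93 uncorrected or .92 corrected | 147–148 | about 164 |
| α .05, power .80, 40% vs 57%, with correction | 147 | 164 |
| α .05, power .90 | 130 (140 corrected) | 145 (156), no match |

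The 10% increase named in Primary Outcomes does not explain the figure either. A rise from 40% to 50% needs 388 per arm uncorrected, and 388/0.9 = 431.1, so 432 after dropout.

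**The case against.** The best defence is that this is a condensed article. Sidedness, choice of formula and handling of multiple outcomes may sit in the full protocol or analysis plan, and their absence here is no fault. The discrepancy is also on the safe side, since more infants are enrolled than the stated 20-point effect needs. Both points are fair, and the second limits the consequence. Neither removes the contradiction: the inputs and the result are printed in the same sentence, and no usual choice of formula or sidedness turns these inputs into 164.

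Three stronger readings are tempting, and the documents do not support them.

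- **That α was really .0125.** Two outcomes at two visits make up to four comparisons, .05/4 = .0125, and 147.8/0.9 = 164.2 is a striking near match. But it also needs an unstated continuity correction, starting from a whole 148 infants it gives 165 rather than 164, and other routes arrive at the same place. It is a plausible explanation and no more.
- **That the printed .05 lets the trial test at four times the intended level.** This assumes an intention to split α that the article nowhere states. If .05 was meant as the overall rate, the sentence would be incomplete rather than wrong.
- **That the trial is underpowered.** For 40% versus 60% at α .05 it is not. On the α .0125 route with continuity correction, power at 148 per arm is about 80%, as printed.

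**Conclusion.** The sample size statement is wrong as written. On a two-sided test at α .05, its inputs support 108 to 119 per arm (216 to 238 in total), not 164 (328). With about 148 evaluable per arm, power for 40% versus 60% is about 92% to 93%, not 80%. At least one printed input is wrong, or one that determines the result is unstated, and the article does not allow a reader to tell which.

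This rests on individual 1:1 randomization, one child per household, and 10% dropout applied once. The 92% to 93% holds only if α is .05 undivided; under a smaller α per comparison the power would be lower. The defect lies in the reported justification and possibly in the α to be used at analysis. It is no reason to change the number enrolled.

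**What to change.** Keep the target of 328 and rewrite the sentence with the inputs actually used: the two rates, α and whether it is split across comparisons, one- or two-sided, continuity correction or not, power, evaluable number per arm, and how dropout was applied.

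- If α is .05 with no split, restate power as about 92% to 93% for 40% versus 60%, naming the version of the formula.
- If a smaller α per comparison was used, state it and the comparisons it covers, and analyse at that level.
- If a different effect or power was used, print that one.

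The sponsor must recover the original calculation. A replacement should not be chosen merely because it lands on 164. The cost is one corrected sentence, with no change to enrolment or procedures. If the recovered calculation used a smaller α, the analysis must also carry that level.

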## Introduction

### Background

Pakistan has an under-5 mortality rate of 69.3 per 1000 live births [1], and is one of the five countries that contributed to half of the under-5 deaths in 2018, with 70% of the deaths being attributed to infectious diseases [2,3]. Pakistan ranks third among countries with the lowest immunization rates for diphtheria-tetanus-pertussis (DTP)–containing vaccine; 40% of children not vaccinated with a 3-dose series of DTP vaccine in 2015 belonged to Pakistan [4]. The low vaccine coverage has led to a number of challenges, including uninterrupted polio transmission and measles outbreaks [5]. In 2013 alone, a measles outbreak resulted in 14,000 cases with 306 deaths [6].

According to the nationwide 2017-2018 Pakistan Demographic and Health Survey (PDHS), 66% of children between the ages of 12 and 23 months had all received the basic vaccines, but only half of the children had age-appropriate vaccines [7]. The yearly PDHS surveys since 1990 have consistently shown that the coverage for age-specific vaccines falls as children grow older, with the highest coverage being seen with the birth vaccine, bacillus Calmette Guérin (BCG) (85%), and the lowest coverage being seen for the 9-month measles-1 vaccine (61%) [8]. In another study, the rate of timely BCG vaccination was 89.3%, with the measles-2 vaccine, given at 15 months of age, having a drop of 2.3% [9]. Low rates of age-appropriate vaccination, even with relatively higher rates of late immunizations, can be extremely detrimental for children as they prolong the duration for which they are vulnerable to illnesses [10].

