#### Randomization

The intervention and control group ratio will be 1:1; the randomization list will be generated through computer assignments with blocks of 6 children; participant allocation will be placed in sealed opaque envelopes that will be opened at the time of enrollment after informed consent.

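### Both primary outcomes name a 10% increase but the sample size assumes 40% to 60%, so the stated power of 0.80 does not apply to the primary target (about 41% for 10 points from a 40% base)

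*Protocol article*

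**What the plan says.** Under Primary Outcomes, the protocol article lists two targets against standard care. The first is "a 10% increase in RCI through a personalized smartphone–based app at 10 and 14 weeks of age". The second is "a 10% increase in RCI within 1 week of the original timeline at 10 and 14 weeks versus standard care". Neither is labelled as percentage points or as a relative change.

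Under Sample Population and Size it states "Target enrollment is 328 infants, 164 in each arm", and that "assumptions used for calculating sample size are an increase in RCI coverage rate from 40% to 60" per cent, with power 0.80, an "α error rate of .05" and "allowing for 10% dropout". Sidedness is not given. Under Randomization, "The intervention and control group ratio will be 1:1".

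The Quantitative Data section describes the primary comparison as the between-arm difference in vaccination status, analysed by intention to treat. It gives no target size. No section links the 10% to the 40%-to-60% assumption.

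**The concern.** The effect that the trial says it aims to see and the effect for which it is sized differ by a factor of two if 10% is absolute (10 against 20 points) and by a factor of five if it is relative (10% against 50%). A reader will take the quoted 0.80 as the chance of detecting the primary target. If the true gain is about 10 points from a control rate near 40%, the trial is more likely than not to give a non-significant result. That result could then be read as showing that the app does not work, although the trial had limited ability to detect the gain it named.

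**Working it through.** **Inputs.** From Sample Population and Size: 164 per arm, control 40%, intervention 60%, power 0.80, alpha .05, dropout 10%. From Primary Outcomes: a 10% increase. From Randomization: 1:1. Evaluable per arm: 164 × 0.9 = 147.6, taken as 148. Assumed because not stated: a two-sided test (z = 1.960; z for 80% power = 0.842).

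**Step 1. The plan's own figure.** With p̄ the mean of the two rates and d their difference,

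n per arm = [1.960·√(2p̄(1−p̄)) + 0.842·√(p1(1−p1) + p2(1−p2))]² / d²

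For 40% versus 60%: [1.960·√0.50 + 0.842·√0.48]² / 0.20² = 96.9, so 97. Dividing by 0.9 gives 107.8, so 108 per arm and 216 in total. With a continuity correction: 107, then 107/0.9 = 118.9, so 119 per arm and 238 in total. One-sided versions are smaller (86 or 96 per arm after dropout). None of these gives 164.

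**Step 2. Power at the planned size.**

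Power = Φ{[d·√n − 1.960·√(2p̄(1−p̄))] / √(p1(1−p1) + p2(1−p2))}

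- 40% versus 60%, n = 148: Φ[(2.433 − 1.386)/0.693] = 93.5%. With all 164: 95.5%.
- 40% versus 50%, n = 148: Φ[(1.217 − 1.379)/0.700] = 40.8%. With all 164: 44.4%.
- 40% versus 44% (relative reading), n = 148: Φ[(0.487 − 1.368)/0.697] = 10.3%. With all 164: 11.0%.
- 40% versus 50%, one-sided .05: 53% (148) to 57% (164).

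From a 40% base, 80% power is reached at about 16 points with 148 per arm (about 15 points with 164). For comparison, 80% power for 40% versus 50% would need 388 evaluable per arm, or 432 after dropout (864 in total).

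**Step 3. What observing exactly +10 points would show (148 per arm, two-sided).** At 40% versus 50%, the standard error of the difference is √[(0.24 + 0.25)/148] = 0.0575. The 95% CI is 10 ± 11.3 points, or −1.3 to +21.3. The pooled test gives z = 1.73, p = .08.

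**Step 4. Dependence on the control rate (148 per arm, two-sided).**

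| Control vs intervention | Power for +10 points | p if exactly +10 is observed |
|---|---|---|
| 40% vs 50% | 41% | .08 |
| 66% vs 76% | 47% | .06 |
| 70% vs 80% | 51% | .047 |
| 75% vs 85% | 58% | .03 |
| 80% vs 90% | 67.5% | .016 |
| 85% vs 95% | 82% | .004 |

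Among these rates, power for 10 points passes 80% only near the ceiling.

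**The case against.** The 10% could be an aspiration rather than the detectable difference. That does not settle the matter: it stands under Primary Outcomes as what the study aims to see, and nothing tells the reader that power was calculated for something else.

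Three stronger readings are tempting, and the document does not support them.

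- *A trial that hits its target exactly must be non-significant.* This holds at a 40% control rate, and at 66% with 148 per arm. With all 164 analysed, 66% versus 76% gives p = .046, and from about 70% upward an observed 10-point gain is significant even with 148 per arm.
- *The 40% base rate contradicts the Background.* That section reports that "66% of children between the ages of 12 and 23 months had all received the basic vaccines", but the same sentence adds that only half had age-appropriate vaccines. The 66% figure concerns basic vaccines at 12 to 23 months. The trial concerns the 10- and 14-week doses, and its second primary outcome is timeliness within one week. The figure of about half is the nearer comparator, and the article describes a further fall with COVID-19. Families at a private hospital who plan to return may well have a higher rate, but the document gives no size for this.
- *Power is 41%, without conditions.* That figure needs an absolute reading, a 40% base and a two-sided test. At a 40% base the readings tried run from about 10% to 57%.

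It is also fair to say that the estimator and interval are usually set out in an analysis plan that is not shown. Their absence is not counted as a fault here. The conflict between the two effect sizes is in the article itself.

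**Conclusion.** Wrong as written. The target in Primary Outcomes and the effect in Sample Population and Size disagree under either reading of 10%, so the stated 0.80 is not the power for the primary target. At a 40% control rate that power is about 41% for 10 points, under the assumptions set out above, and every other reading tried at that rate is also well below 80%. Separately, 328 does not follow from the stated inputs: it exceeds the 216 to 238 they require and gives about 93% power, not 80%, for 40% versus 60%. The 41% figure uses the planned enrolment itself, so this second discrepancy does not alter it. Whether an observed 10-point gain would be significant depends on the control rate, which the document does not establish for this centre.

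**What to change.** No added enrolment is needed.

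1. Reconcile Primary Outcomes with Sample Population and Size on one target difference, and say whether it is absolute or relative.
2. Replace the power statement with what 328 delivers under stated assumptions, including sidedness: about 93% for 40% versus 60%, 80% for about 16 points from a 40% base, and about 41% for 10 points. Alternatively, correct the inputs that produced 328. It is not enough to add that the trial is sized for 20 points, because that beside a power of 0.80 would leave the second discrepancy in place.
3. Show power for the chosen target across a range of control rates, as in the table above. If the no-show study or the earlier 3300-child study is used to choose that range, say which centre its rates come from, since the article does not say that either gives this centre's own rate.
4. Conclude from the risk difference with its 95% CI, so that a non-significant result is not read as excluding a 10-point benefit.

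The cost is revised wording and a short table. The downside is that the stated power for a 10% gain becomes less favourable. Enrolment was in process when the article was written, so the restated figures should be dated and fixed before any comparison by arm.

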#### Sampling Methodology

The study staff will approach families visiting the AKUH CHC vaccination center, who have brought an infant for their 6-week RCI. Staff will explain the study objectives to the parents or caregivers. If the parent or caregiver is interested in the study, the infant will be evaluated for enrollment. One child per household will be selected. In a household where there is more than one child due for a 10- or 14-week vaccination, a random selection will be made by a program designed in the mobile phone device. After meeting the eligibility criteria, informed consent will be obtained, and the infant will be enrolled in the study.

#### Randomization

The intervention and control group ratio will be 1:1; the randomization list will be generated through computer assignments with blocks of 6 children; participant allocation will be placed in sealed opaque envelopes that will be opened at the time of enrollment after informed consent.

### Data Analysis

#### Qualitative Data

The data will be transcribed into a written form from audio recordings and will be analyzed via the qualitative data analysis software NVivo 11 (QSR International). Written transcripts will then be uploaded into NVivo 11 software to offer easy and organized retrieval of data for analysis. The data analysis will be conducted according to discourse analysis to identify the themes and subthemes conveying the underlying conscious or unconscious intent of the caregivers through language. The interview guides will also be pretested in a similar community.

#### Quantitative Data

Analyses will be conducted according to the intention-to-treat principle. The primary outcome is to assess the difference in vaccination status between the intervention and control arms. The chi-square test will first be used to compare sample characteristic proportions between the groups.

### Exit Survey

A second survey will be conducted when the child visits the CHC vaccination center for their 14-week CRI or at 18 weeks of age, whichever comes first. If the caregiver did not visit the facility at 14 weeks, they will be phoned when their child reaches 18 weeks of age to complete the exit survey in order to identify their vaccination coverage according to the schedule, to be confirmed by physical examination of their EPI card.

### Ethical Considerations

The study protocol and associated study instruments, including consent forms in English and local languages, have been approved by Aga Khan University’s Ethics Review Committee. The study will be conducted in accordance with the Declaration of Helsinki and established guidelines. All participants will provide informed consent before participation. Participants will have the right to refuse to participate in the study or leave the study at any time; this will not affect any services provided to them at the health center. Data confidentiality will be maintained at all times. No personal identifiers will be used in any reports or publications of the study.

### Data Management, Confidentiality, Privacy Protection, and Quality Assurance

The audio recording and transcripts will have unique identifiers; original and backup files will be archived in a password-protected computer system at Aga Khan University. Only transcripts and themes will be shared at NED University and the University of Surrey without nominative information. All study-related data including the recordings will be stored in an encrypted server with password protection and will only be accessible by the study-specific personnel.

Baseline and follow-up data will be collected on a smartphone device via a survey. The entry program will be designed to capture data as well as the location of the interviewer along with some monitoring parameters. Each child participant will be given a structured unique identifier. Business rules; skips, using skip logic; and consistency checks will be incorporated, and important fields will be marked as *must enter* in the questionnaire to maintain data collection quality. The database will reside on a central computer at Aga Khan University, which will be managed by the study staff. A web-based dashboard will be designed to report daily study progress. Mobile phone numbers will not be shared except to track and analyze patterns of use. Only relevant study staff will have access to study the data that has been allowed by the local ethics committee. All study staff will undergo basic research ethics training. Participants’ information will be given a study code, and no personal identifiers will be shared. Data confidentiality will be maintained at all times. No personal identifiers will be used in any reports or publications of the study. No individual identifiers, such as names of participants or their locations, will be shared. In addition, a confidentiality agreement has been signed with the universities stating that the ID numbers provided will only be used for the trial. All audio recordings will be destroyed within 5-7 years of the study, according to the recommendation of the AKUH ethics committee.

